#### Interim analyses

This randomized trial does not incorporate interim analyses to stop the study for futility. Coming from experience, we neither assume not to reach the full planned sample size nor that early data would suggest that an important treatment effect is unlikely to be found, even if the study continues to its full planned sample size.

#### Methods for additional analyses

We will analyse the effect of sociodemographic and clinical variables on the primary outcome as well as the effect of periods of fasting and calorie intake. Additionally, stratified analysis will be performed for those who completed t2 and t3 follow-up. All statistical tests assume a two-sided significance level of 0.05.

#### Methods in analysis to handle protocol non-adherence and any statistical methods to handle missing data

We use the ITT approach; all randomized patients are included in the analysis, based on the groups to which they were initially randomly assigned. To assess the bias of your data due to non-response, we will perform a non-response bias analysis.

#### Plans to give access to the full protocol, participant level-data and statistical code

There are no plans to grant access to full protocol, participant-level dataset or statistical code.

### Oversight and monitoring

#### Composition of the coordinating centre and trial steering committee

All investigators are steering committee members, including an external independent expert member. Investigator meetings are held regularly to monitor and supervise the progress of the study towards its short-term and overall objectives and adherence to the protocol.

#### Composition of the data monitoring committee, its role and reporting structure

We did not implement a special data monitoring committee, because the members of the data research team working on data management are well versed. We performed internal monitoring to verify data within the constraints of the regulatory requirements two times during the data collection phase. A data monitoring committee was not considered as this was a low-risk intervention co-investigator meetings including auditing trial conduct which was held monthly during the recruitment phase and then quarterly.

#### Adverse event reporting and harms

It is the responsibility of the investigators to report serious adverse events. An adverse event is defined as any untoward medical occurrence in a subject without regard to the possibility of a causal relationship. Adverse events will be collected after the subject has provided consent and enrolled in the study. All adverse events occurring after entry into the study and until rehabilitation discharge will be recorded.

Based on our experience with comparable trials, no adverse events related to the intervention are expected.

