### Objectives

To date, evidence suggests that intermittent fasting can be an effective way to improve health and well-being, but more research is needed to fully understand its long-term effects [16, 22]. Only few studies document longer periods of fasting in high-risk person such as rehabilitation patients. Therefore, the aim of the ongoing InterVFast trial is to investigate the effectiveness of intermittent fasting amongst cardiac rehabilitation patients after 4-week inpatient rehabilitation as well as 3 and 12 months subsequently including patients’ perspective.

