### Outcomes

The primary outcome of this study is difference in weight loss between baseline and end of inpatient rehabilitation after 4 weeks (short-term effectiveness). Secondary outcomes are difference in weight loss between baseline and 3 and 12 months after inpatient rehabilitation (long-term effectiveness), changes in blood pressure, fasting blood glucose and lipids and changes in diet as well as patients’ acceptance.

Weight, blood samples and clinical data are routinely collected as part of the initial and final examination. During inpatient rehabilitation, participants note daily periods of fasting as well as practicability (rating scale from 0 — very bad to 5 — very easy) in a fasting diary. They record all food and drinks, type of meal (breakfast, lunch, dinner, or snack), type of food and portion size. In addition, we carry out interviews about perceived advantages and disadvantages and acceptance with all participants in the IG.

After initial examination at admission (baseline, t0), three follow-up times are provided: final examination at the end of inpatient rehabilitation after 4 weeks (t1), as well as two follow-up times after inpatient rehabilitation after 3 and 12 months. The World Health Organization-Five Well-Being Index (WHO-5) is used for self-reported measure of current mental wellbeing at t0 and t1. A standardized follow-up examination (weight, blood samples) will be carried out by the family doctor at t2 and t3 for valid information. A financial incentive will be paid to family doctors for examination and data transfer.

Sociodemographic characteristics and comorbidities at baseline will be collected as moderating variables. Stable covariables (e.g. sociodemographic characteristics) will be collected only at baseline, while changeable variables will be measured at baseline and follow-up.

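### Adverse-event recording stops at rehabilitation discharge, so clinical events are not systematically collected during the 12 months of the long-term secondary outcomes

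*Protocol article*

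**What the plan says.** The section Adverse event reporting and harms of the protocol article defines the events broadly: "An adverse event is defined as any untoward medical occurrence in a subject without regard to the possibility of a causal relationship". It then sets both ends of the recording period: "All adverse events occurring after entry into the study and until rehabilitation discharge will be recorded". Serious events have a separate sentence with no end date and no route of collection: "It is the responsibility of the investigators to report serious adverse events". The section adds that "no adverse events related to the intervention are expected".

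Outcome follow-up runs much longer. After the assessment at the end of the 4-week stay (t1), the Outcomes section provides for two more, t2 and t3: "as well as two follow-up times after inpatient rehabilitation after 3 and 12 months". On their content it says: "A standardized follow-up examination (weight, blood samples) will be carried out by the family doctor at t2 and t3 for valid information". The abstract and the section on assessment and collection of outcomes describe that examination in the same way.

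The Objectives justify the trial by a gap in evidence: "Only few studies document longer periods of fasting in high-risk person such as rehabilitation patients". The Discussion names long-term maintenance as a focus.

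**The concern.** The harms window and the outcome window do not match. The article sets out to study effectiveness to 12 months after rehabilitation in patients it regards as high-risk, yet it closes the record of untoward events when they go home. This is a stated cut-off, so it cannot be put down to detail left to an analysis plan or a fuller protocol.

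Two things are at stake.

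- **Reporting.** A weight difference at 3 or 12 months would be published without systematic information, from the same period, on death, admission or cardiovascular events in either arm.
- **Missing data.** These events are plausible reasons for a missing or altered t2 or t3 weight. A patient who has died has no 12-month weight, which is different from a patient who did not return. The article plans an intention-to-treat analysis, a non-response bias analysis and a separate analysis of those who completed t2 and t3. None of these can tell the two situations apart unless the events are recorded.

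**Working it through.** The article gives no figure for harms, so there is none to reproduce, and the sample-size calculation does not enter. The check compares the two windows and then asks what the difference amounts to.

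**1. Inputs**
- Recording window: study entry to discharge, about 4 weeks (Adverse event reporting and harms; length of stay from Intervention description).
- Follow-up: 12 months after rehabilitation (Outcomes), that is 365.25 / 7 = 52.18 weeks.
- Patients: 120 consented (Trial status). Arm sizes are not given, so 60 per arm is an assumption. The planned 50 per arm (Sample size) is shown as the lower case.

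**2. Share of observation time with adverse-event recording**

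4 / (4 + 52.18) = 4 / 56.18 = 7.1%, leaving 92.9% outside the window.

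**3. Person-years per arm, assuming no loss to follow-up**

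Person-years = n × weeks / 52.18. If no event is seen, the approximate 95% upper bound on the rate is 3 / person-years (rule of three).

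| n per arm | Recording to | Person-years | Upper bound per person-year |
|---|---|---|---|
| 60 | discharge | 60 × 4 / 52.18 = 4.6 | 3 / 4.6 = 0.65 |
| 60 | t3 | 60 × 56.18 / 52.18 = 64.6 | 3 / 64.6 = 0.046 |
| 50 | discharge | 50 × 4 / 52.18 = 3.8 | 0.78 |
| 50 | t3 | 50 × 56.18 / 52.18 = 53.8 | 0.056 |

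**4. Expected events per arm of 60**

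The article gives no event rate. The rates below are assumptions, taken as constant over time.

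| Assumed annual rate | During the stay (60 × rate × 4 / 52.18) | In the 12 months after discharge (60 × rate) |
|---|---|---|
| 2% | 0.09 | 1.2 |
| 5% | 0.23 | 3 |
| 10% | 0.46 | 6 |

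Under any of these rates, nearly all events would fall after recording has ended. The counts are still small, too few for a between-arm test of safety even at 10%.

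**5. Is there another route to these events after discharge?**
- The t2/t3 examination is described as weight and blood samples.
- The serious-event sentence is open-ended, but it does not say how an investigator would learn of an event at home.
- The section on participant retention mentions a survey at t2 and t3 whose content is not shown, and Outcomes says changeable variables are measured again at follow-up. Neither mentions clinical events.

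Systematic collection is therefore not described anywhere, although incidental reporting remains possible.

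**The case against.** The strongest reply is that the window fits the treatment. The fasting programme is delivered during the 4-week stay, and no fasting is prescribed afterwards. Recording harms over the treatment period is a recognised design choice, and the primary outcome at 4 weeks lies inside it. This stands, and it limits the consequence to the secondary, long-term part of the trial. It does not remove the mismatch, because the article itself extends its question to 12 months.

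Four stronger readings are tempting, and the article does not support them.

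- **That the trial can say nothing about longer-term safety.** Blood samples are taken at t2 and t3, and the duty to report serious events has no end date.
- **That events after discharge are certainly not captured.** The family-doctor form and the survey are not shown. What can be said is that no systematic capture is described.
- **That the article contradicts itself on risk, or claims long-term safety.** The Objectives call the patients high-risk. The monitoring section calls the intervention low-risk: "A data monitoring committee was not considered as this was a low-risk intervention". These are different things and can both be true. The Discussion makes no long-term safety claim, and its remark on practicability has no time horizon.
- **That the 12-month weight comparison cannot be interpreted.** A non-response bias analysis is planned. Knowing the events would improve it, but nothing shows that the comparison fails without them.

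It is also fair to say that 7% measures calendar time and not harm, and that any added data would be descriptive only.

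**Conclusion.** The point holds in a limited form. Adverse-event recording covers about 7% of each patient's time in the trial, and no systematic collection of deaths, admissions or cardiovascular events is described for the other 93%. The trial could therefore not systematically report clinical events over the period of its long-term weight outcomes, or separate them from ordinary non-response at t2 and t3. The 4-week primary comparison and the harms record for the delivered programme are unaffected.

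The 7% rests only on the article's own schedule. The person-year figures also assume 50 or 60 patients per arm and no loss to follow-up, and the event counts assume 60 per arm and annual rates of 2% to 10%.

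**What to change.** Amend the section Adverse event reporting and harms so that death, hospital admission and cardiovascular events since the last contact are recorded in both arms at t2 and t3. A short item on the existing family-doctor examination would do, since the doctors are already paid for that examination and the data transfer. For patients already past t2, ask retrospectively at t3. Report the events descriptively by arm and use them in the planned non-response analysis.

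The costs are an amendment notice, a check that the existing consent covers these data, and less complete recall of earlier events. There will be too few events for a between-arm safety test, and none should be promised.

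If the change is not made, state in the article and in the trial reports that adverse events cover the inpatient phase only, and draw no safety conclusion for the time after discharge.

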#### Frequency and plans for auditing trial conduct

To assess and assure the reliability and integrity against all relevant written standards, a systematic internal examination is conducted twice a year (three times in total). We will verify the following variables for all patients: initials, date of birth, sex, signed informed consent, eligibility criteria, date of randomization, treatment assignment, adverse events and endpoints. The process is independent from the funder.

#### Plans for communicating important protocol amendments to relevant parties

Important protocol modification changes will be reported to the ethical committee and other relevant parties.

#### Dissemination plans

We developed a publication strategy to select appropriate content, formats and audiences. The trial results will be reported to participants and the public in a public-centred research report. Healthcare professionals and the scientific community will be informed via peer-reviewed journal publications and conference proceedings.

According to the guiding principle of the PI’s affiliation, research publications are not influenced or controlled by funders or investigators. We will publish both positive and negative outcomes in an equitable manner.

## Discussion

For the first time, the InterVFast intervention systematically investigates shot term as well as long-term effects of intermittent fasting on weight loss and cardiovascular health outcomes within a cardiac inpatient rehabilitation sample. Compared to other weight-loss intervention studies, our approach addresses patients with CHD and focuses on patients’ acceptance and long-term maintenance. However, since men are underrepresented relative to women in current research concerning lifestyle changing interventions, this trial enriches the existing state of research.

Yet — if proven effective — the findings of this study could strengthen the idea that intermittent fasting may be a practicable intervention. Beyond the cardiac rehabilitation context, the InterVFast intervention could be model for other chronic conditions and medical settings. Future research should explore the effectiveness of intermittent fasting in both premenopausal and postmenopausal women with CHD and provide evidence of the effectiveness of maintenance strategies considering factors that help to promote patients’ motivation.

### Trial status

The trial is ongoing. The recruitment of participants started on 23 March 2022 and was completed on 14 September 2022. A total of 278 of 352 patients screened met inclusion criteria, and 120 were willing to participate and gave informed consent.Recruitment status and baseline evaluation: CompletedFollow-up status t1: CompletedFollow-up status t2 and t3: Ongoing

## Data Availability

There are no plans to grant access to full protocol, participant-level dataset, or statistical code.

## Abbreviations

ANOVA: Analysis of variance
BMI: Body mass index
CHD: Coronary heart disease
IMIBE: Institute for Medical Informatics, Biometry and Epidemiology
IG: Intervention group
CG: Control group
NYHA: New York Heart Association Classification
RCT: Randomized controlled trial
WHO-5: World Health Organization-Five Well-Being Index
